**Methods:**

This study has a cross-sectional, binational design and is part of the “Barefoot Locomotion for Individual Foot- and health Enhancement (Barefoot LIFE)” project. Two large cohorts (n_(total)_ = 520) of healthy children and adolescents between 6 and 18 years of age will be included respectively in Germany and South Africa. A barefoot questionnaire will be used to determine habitually barefoot individuals. The testing will be school-based and include foot mechanical (static arch height index, dynamic arch index, foot pliability) and motor performance (coordination, speed, leg power) outcomes. Gender, BMI and level of physical activity will be considered for confounding.

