### Study design

This is a binational multicenter, cross-sectional observational study looking at differences of foot mechanics and motor performance between habitually barefoot and habitually shod children and adolescents aged 6–18 years. Ethical approval has been obtained from the ethics committee of the medical association Hamburg (protocol number PV4971) and Stellenbosch University ethics committee (protocol number HS1153/2014). The regional separation of the recruitment is due to the obligation of footwear use in most German educational institution while in South Africa the habit of being barefoot prevails.

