### Testing procedure

Methodological planning stipulates all anthropometrical, foot and motor performance measurements to be performed during a physical education lesson. Prior to the testing, a physical activity questionnaire for children/adolescent (PAQ-C and PAQ-A [25, 26]) and a barefoot questionnaire will be distributed by the teachers and collected by the study staff on the testing day and briefly checked for completeness. All children bringing the signed consent form and voluntarily want to participate will be gathered and all relevant information for the testing will be given by the principal investigator. After a short warm up period (jogging for < 5 min), participants will be randomly allocated to the seven testing stations:AnthropemetryFoot caliperPressure plate20 m sprintingLateral jumpingStanding long jumpBackwards balancing

After their first testing station, a participant will be transferred to the next vacant station without a fixed order. Testing station 1–3 will be completed only barefoot, while testing stations 4–7 will be performed in barefoot and shod conditions. The order of the condition is randomized a priori on the registration sheet which is distributed to the participants on the testing day. A flowchart displaying the participant flow through the study is shown in Fig. 1.

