### Barefoot questionnaire

Participants will complete a six-item questionnaire used to decide if a child can be considered barefoot or shod. This questionnaire (Additional file 2) is developed specifically for this study and inquires if the child is barefoot on a three point Likert scale: most of the time, half of the time or barely/none of the time during 1) school 2) sports and 3) in and around the house. These questions will be asked twice: one for the warm weather and one for cold weather. For those in secondary school, questions are repeated for when they were in primary school. Due to the multi lingual culture of South Africa, the questions will be asked in Afrikaans, English and Xhosa. Children will be considered barefoot when they are always barefoot in and around the house and always barefoot in school *or* during sports -in warm weather- in primary school. In secondary school they have to have a similar level of barefootness during primary school *and* are always barefoot in and around the house currently.

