### Statistical analysis

Descriptive data will be presented using descriptive statistics. The participant’s barefoot questionnaire and the PAQ outcomes will be compared to all attending children in 2 primary (1 rural, 1 urban) and 2 secondary schools to assess external validity. The outcome measures will be evaluated for normality using Shapiro-Wilkins and visually using P-P plots, if possible, non-normal distributed data will be adjusted. Mixed Models linear regression will be used to assess if the foot mechanical and motor performance outcomes differ between the barefoot and the shod participants (fixed factors). Furthermore, we will test differences due to being barefoot or shod change by age by adding an interaction of age*group to the linear regression. Differences in foot strike pattern during jogging and sprinting between barefoot and shod participants will be assessed using ordinal regression. The school of a participant will be added to the model as a random effect in order to adjust for possible differences between the schools and their geographical location. Furthermore, Gender, BMI, PAQ-Score, ethnicity and inside/outside testing will be tested for confounding in all models (regression coefficient changes >10 %). We hypothesize that older boys could have higher arches (lower dAI) [37] and perform better on motor performance tasks, while girls’ feet will show a higher pliability. BMI increases the dAI and possibly decreases motor performance [38, 39]. A higher level of physical activity (higher PAQ score) is probably related to better motor performance. And lastly, Caucasians could have higher arches (lower dAI) [40].

We anticipate that gender might modify the effect of being barefoot or shod on the outcome measures and therefore gender will additionally tested as an effect modifier (interaction between outcome and gender *p* < 0.1). In all cases, a significance level of 5 % is pre-stipulated.

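### Activity (and BMI for motor outcomes), measured at testing after long exposure, is screened by a 10 % change rule that cannot tell a confounder from a mediator, so part of any barefoot effect may be adjusted away

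*Protocol article*

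**What the plan says.** The Study design section of the protocol article states: "This is a binational multicenter, cross-sectional observational study". The stated aim (Background, last paragraph; Discussion) is the effect of being habitually barefoot on foot mechanics and motor performance, and the abstract calls this a long-term effect.

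The covariate rule is in Statistical analysis: "Gender, BMI, PAQ-Score, ethnicity and inside/outside testing will be tested for confounding in all models". The criterion in brackets is "regression coefficient changes >10" %. The abstract gives activity and BMI the same single role: "Gender, BMI and level of physical activity will be considered for confounding". Only gender receives a second role, as an effect modifier. The same section expects that "A higher level of physical activity (higher PAQ score) is probably related to better motor performance" and that BMI may lower motor performance.

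On timing, Testing procedure says that "a physical activity questionnaire for children/adolescent (PAQ-C and PAQ-A [25, 26]) and a barefoot questionnaire will be distributed by the teachers" before the test day and plans for "all anthropometrical, foot and motor performance measurements to be performed during a physical education lesson". No earlier value of activity or BMI is described. The exposure reaches further back. For older pupils the Barefoot questionnaire section says: "In secondary school they have to have a similar level of barefootness during primary school". It adds a second condition, that they are still always barefoot in and around the home.

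For BMI and the dynamic arch index (dAI), the Discussion (Foot mechanics) gives a separate reason to adjust: fat tissue may alter the footprint, so adjustment is meant to improve the validity of the measure.

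**The concern.** A confounder should be adjusted for when the target is the effect of a long-standing habit. A mediator should not be if the target is the total effect, and a consequence of the outcome should not be at all. Current activity could be any of the three. Climate or school culture may drive both activity and barefootness, growing up barefoot may change how active a child is, and skilled children may choose to be more active. For motor outcomes BMI could likewise be a confounder or a mediator.

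A change-in-estimate rule looks only at whether the group coefficient moves. A confounder moves it, and so does a mediator of any importance. The rule therefore decides whether the reported coefficient is a total difference or one with the activity path removed, on a criterion that carries no information about which is wanted. Because it is applied model by model, PAQ could be kept for the sprint and left out for lateral jumping, and coefficients shown side by side would then not estimate the same quantity.

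What is at stake is how the group coefficient for motor performance can be read, since the article presents it as a long-term effect of being habitually barefoot.

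**Working it through.** The plan gives no figure for this bias, so the check is illustrative.

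**Inputs from the documents**
- Retention threshold: relative change in the group coefficient above 10 % (Statistical analysis).
- Sample: 13 years of age × 20 children × 2 countries = 520, which matches the stated total and gives 260 per country. The check takes 260 per exposure group, which assumes that exposure follows country.

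**Assumptions, not in the documents**
- a = shift in PAQ caused by barefoot habit: 0.2 to 0.4 SD.
- b = change in motor score per SD of PAQ: 0.2 to 0.3 SD.
- T = total barefoot effect on motor score: 0.3 SD.
- PAQ is a pure mediator, with no clustering by school and no confounding.

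**Expected attenuation**
In a linear model, adding the mediator lowers the group coefficient from T to T − a×b. The relative change is a×b / T. The rule is met in expectation when a×b > 0.10 × 0.3 = 0.03 SD.

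| a | b | a×b removed (SD) | share of T | adjusted estimate (SD) | PAQ kept by the rule |
|---|---|---|---|---|---|
| 0.2 | 0.2 | 0.04 | 13 % | 0.26 | about 69 % |
| 0.2 | 0.3 | 0.06 | 20 % | 0.24 | about 88 % |
| 0.4 | 0.2 | 0.08 | 27 % | 0.22 | about 98 % |
| 0.4 | 0.3 | 0.12 | 40 % | 0.18 | about 100 % |

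The last column comes from simulating 260 against 260 under these assumptions and applying the rule to each simulated data set. All four values of a×b exceed 0.03, so the rule is met on average. In single samples it is not always met, which is why the retention rate starts near 69 %.

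**A second parameterisation**
Holding the direct effect at 0.3 SD and letting the total be 0.3 + a×b gives the same picture. At a = 0.3 and b = 0.3 the total is 0.39 and adjustment brings it to 0.30, a loss of 0.09 / 0.39 = 23 %. Across a = 0.1 to 0.5 and b = 0.2 to 0.3 the share lost runs from 0.02 / 0.32 = 6 % to 0.15 / 0.45 = 33 %. Retention was 24 to 47 % at a = 0.1, 60 to 81 % at a = 0.2, 87 to 97 % at a = 0.3 and 99 to 100 % at a = 0.5.

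**No barefoot effect on PAQ (a = 0)**
The mean estimate is 0.30 with and without PAQ, so there is no systematic shift. The rule still kept PAQ in 13 % (b = 0.2) to 27 % (b = 0.3) of runs through chance imbalance. Selection can therefore differ between motor tests even when PAQ has no causal link with barefootness.

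No comparable figure is offered for BMI. The argument about the rule applies to it, but the illustration is for PAQ only.

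**The case against.** A reader might infer that the plan does adjust away part of the barefoot effect. The documents do not support that. They state paths from activity and BMI to the outcomes, but nowhere say that barefootness changes activity or BMI, or that motor skill drives activity. Without a barefoot effect on PAQ, nothing systematic is lost through mediation.

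True confounding is at least as plausible. Recruitment is split by country because footwear habits are, and the Discussion attributes those habits to climate and culture. Either could change activity and BMI by a route that has nothing to do with bare feet, and leaving both out would then bias the comparison. This stands. It rules out simply declaring the unadjusted model correct.

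The timing is also less clear-cut than it may seem. The secondary-school definition requires current barefootness at home as well as the primary-school history, and primary pupils are classified on present behaviour, which can include sport. Exposure and activity are partly concurrent. This weakens any claim that PAQ must come after exposure, but it does not establish that PAQ comes before it.

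Two further points stand in part. Only children active for at least 120 minutes a week are eligible, so dropping PAQ from the model does not recover a total effect in all children. And where the rule leaves PAQ out, adding it to that model would have moved the coefficient by no more than 10 % in that sample, so the inconsistency between tests is bounded there. It is not bounded where PAQ is kept.

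Finally, the rule already requires fits with and without each covariate, and a condensed article may leave their reporting to a fuller plan. That makes the fix cheap. It does not repair the rule that the article fixes for choosing between them.

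**Conclusion.** The point holds as a conditional one. For motor outcomes, PAQ and BMI are measured at testing and could play more than one causal role. A 10 % change rule cannot tell the roles apart, so a single coefficient selected by it cannot be read as the long-term effect of being habitually barefoot. Part of any such effect may be adjusted away, and the selection may differ between motor tests.

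The size is unknown from the documents. Under the assumed ranges the loss is 0.04 to 0.12 SD, or 13 to 40 % of a 0.3 SD total effect, with PAQ kept in about 69 to 100 % of samples. It is zero on average if barefoot habit does not change PAQ. The figures rest on a pure mediator, 260 per group and no clustering or confounding.

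The point does not extend to BMI in the dAI model, where the article gives a measurement reason for adjusting. Nor does it show that the model without PAQ and BMI is the right one.

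**What to change.** In Statistical analysis, take PAQ, and BMI for motor outcomes, out of the 10 % rule. For every motor outcome report the group difference from the same two pre-specified models, one without PAQ and BMI and one with both, all other terms being equal.

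State in advance how each is read:
- **Without PAQ and BMI:** the total difference among eligible children, open to confounding by activity and BMI between the countries.
- **With PAQ and BMI:** the difference not passing through activity or BMI. This reading also assumes that activity is not itself a result of motor skill.

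Claim a long-term barefoot effect on motor performance only in the light of both. Keep BMI in the dAI model for the reason already given in the Discussion.

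No new data are needed. The cost is a change of wording, one extra reported model per motor outcome, and a less simple conclusion if the two models disagree.

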**Fig. 3 Fig3:**
[figure not shown]
Heel to toe length, foot width and dorsum height measurements will be obtained using a specially constructed platform. Dorsum height will be measured at 50 % of the heel to toe length using the sliding caliper pictured on the right foot in this picture. Static arch height index will be defined as the ratio of dorsum height and heel to toe length

$$ Static\  arch\  height\  index = \frac{Dorsum\  height}{Heel-to- toe\  length} $$

Feet of the participants will be measured at sitting (10 % of body weight (BW)) and standing (50 % of BW) and the pliability ratio will be calculated according to Kadambande et al. [20]:$$ Pliability\  ratio = \frac{HTL\ 50\%\  of\ BW \times FW\ 50\%\  of\ BW}{HTL\ 10\%\  of\ BW \times FW\ 10\%\  of\ BW} $$

Foot strike patterns will be captured during 20 m jogging and both sprinting trials in each condition at the 17.5 m mark using a wide-angle high speed camera (GoPro HD Hero 4, GoPro Inc., San Mateo, California, USA). The camera will be positioned 150 cm from the midline orthogonal to the marked running way and set to record 120 frames per second at a resolution of 1280 × 720 pixels. After testing, videos will be processed using a video editing software (Adobe Premiere Pro CS 6, Adobe Systems, San Jose, California, USA) and rated independently by two reviewers, with a third experienced reviewer for consensus. A rearfoot strike is defined as a first ground contact with the heel or the rear third of the foot, while a forefoot strike is present when the anterior part of the foot first contacts the ground. For a midfoot strike heel and anterior part of the foot contact the ground simultaneously. This method has been used successfully in other studies to determine the foot strike pattern [33].

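### The 10 % coefficient-change rule covers all models, but in the ordinal foot-strike models it mixes confounding with a scale shift and can drop a real confounder

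*Protocol article*

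**What the plan says.** All of this is in the protocol article, Methods/Design, Statistical analysis, unless another place is named.

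- **Candidates and rule.** "Furthermore, Gender, BMI, PAQ-Score, ethnicity and inside/outside testing will be tested for confounding". The scope and threshold follow: "ethnicity and inside/outside testing will be tested for confounding in all models (regression coefficient changes" above 10 %). No model is exempted.
- **Foot strike.** "Differences in foot strike pattern during jogging and sprinting between barefoot and shod participants will be assessed using ordinal regression". The link is not stated. The Foot mechanics section defines rearfoot, midfoot and forefoot strikes, so the outcome has three categories.
- **Other outcomes.** "Mixed Models linear regression will be used to assess if the foot mechanical and motor performance outcomes differ" between barefoot and shod participants.
- **Clustering.** "The school of a participant will be added to the model as a random effect".
- **Ethnicity elsewhere.** The Discussion (Barefoot questionnaire) says that ethnicity will be added to the analyses as a confounder. It mentions no screening step.

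The covariate directions hypothesised in the Statistical analysis section concern arch, pliability and motor performance. None concerns foot strike.

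**The concern.** A change-in-coefficient rule works only if the coefficient stays put, on average, when a covariate that is no confounder is added. That holds for the linear mixed models: a covariate balanced between barefoot and shod children leaves the group difference unchanged in expectation. It does not hold for a log odds ratio. Adding any predictor of foot strike moves the coefficient away from zero, even with perfect balance. So in the ordinal models the observed change has two parts, and the rule sees only their sum.

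When confounding exaggerates the barefoot effect, adjustment pulls the coefficient down while the scale shift pushes it up. The two can cancel. The rule then leaves the confounder out, and its bias is reported as an effect of being barefoot. The study is observational and exposure largely follows country (Study design), so covariate adjustment is its main stated protection against this.

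**Working it through.** The 10 % threshold is a chosen rule, so the plan has no figure to reproduce. The check asks what the rule would do in an ordinal model.

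**Assumptions (not in the documents).** Proportional odds with a logit link; group log odds ratio 0.8; equal groups; about 60% rearfoot strikes at the reference and 80% cumulative at the second cut-point; one normal covariate; no school effect. Change = (adjusted - crude)/crude.

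**Step 1: balanced covariate, large sample.** There is no confounding here, so the whole change is scale shift.

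| Covariate log-odds effect per SD | 0.2 | 0.3 | 0.4 | 0.5 | 0.6 | 0.8 | 1.0 |
|---|---|---|---|---|---|---|---|
| Change | +0.9% | +2.0% | +3.6% | +5.5% | +7.8% | +13.4% | +20.0% |

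The 10 % line is crossed near 0.7 per SD. The exact cut-point matters little: another fit gives crude coefficients of 0.704 and 0.665 at 0.8 and 1.0 per SD, so 0.8/0.704 - 1 = 13.6% and 0.8/0.665 - 1 = 20.3%.

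A balanced binary covariate has SD 0.5, so 0.8 to 1.0 per SD means an odds ratio of exp(1.6) = 5.0 to exp(2.0) = 7.4. Direct fits with a binary covariate give +2.8% at odds ratio 2, +7.2% at 3, +11.8% at 4 and +16% at 5.

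**Step 2: real confounder acting away from the null.** With covariate effect b and imbalance d (in SD), confounding alone would give a crude coefficient of 0.8 + b × d, as in a linear model. Its change is 0.8/(0.8 + b × d) - 1. Multiplying that ratio by the scale-shift factor from step 1 reproduces the fitted ordinal change. For b = 0.8 and d = 0.15: 0.8/0.92 = 0.870, and 0.870 × 1.134 = 0.986, that is -1.4%.

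| b per SD | d (SD) | Confounding alone | Ordinal coefficient change | Crude rearfoot difference overstated by |
|---|---|---|---|---|
| 0.6 | 0.15 | 0.8/0.89 - 1 = -10.1% | -3.1% | 11.0% |
| 0.6 | 0.20 | 0.8/0.92 - 1 = -13.0% | -6.3% | 14.7% |
| 0.8 | 0.15 | 0.8/0.92 - 1 = -13.0% | -1.4% | 14.7% |
| 0.8 | 0.20 | 0.8/0.96 - 1 = -16.7% | -5.6% | 19.6% |
| 1.0 | 0.15 | 0.8/0.95 - 1 = -15.8% | +1.1% | 18.5% |
| 1.0 | 0.20 | 0.8/1.00 - 1 = -20.0% | -4.0% | 24.6% |

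In all six rows the confounding alone passes 10 %, and the ordinal change does not.

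**Step 3: where the rule still works.** At 0.8 per SD the change is -12.8% for an imbalance of 0.30 SD, -24.5% for 0.50 SD and -43% for 1.0 SD. If the confounder acts toward the null, the two parts add up: +42% at 0.8 per SD and 0.20 SD.

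**Step 4: with sampling error.** Simulations at N = 520, the total in the abstract, used a binary covariate. The comparator applies the same rule in a linear model on the latent outcome.

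| Scenario | Group OR | Covariate OR | Ordinal | Linear |
|---|---|---|---|---|
| Balanced, kept | 2 | 2 | 11% | 5% |
| Balanced, kept | 3 | 5 | 76% | 13% |
| Away from null (prevalence 40% v 60%), dropped | 2 | 2 | 19% | 10% |
| Away from null, dropped | 3 | 2 | 65% | 40% |
| Away from null, dropped | 3 | 3 | 41% | 5% |
| Away from null, dropped | 3 | 5 | 34% | 0% |
| Toward null, kept | 3 | 2 | 89% | 80% |

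**The case against.** A reader might infer that in the foot-strike models the rule generally keeps non-confounders and drops real ones. The documents do not support that. They give no covariate effect on foot strike, and the checks show no such general pattern:

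- A balanced covariate of weak or moderate strength moves the coefficient by under 8%. Passing 10 % takes about 0.7 per SD, or a binary odds ratio between 3 and 4.
- Masking needs confounding away from the null and a modest imbalance. Inside/outside testing and ethnicity probably differ between countries by more than 0.20 SD: the Discussion expects mostly outdoor sprinting in South Africa and an ethnic discrepancy between the cohorts.
- Keeping a balanced predictor gives a valid odds ratio conditional on it. That is a change of scale, not a bias.

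A reader might also infer that different covariate sets would spoil a comparison of jogging with sprinting. No such comparison is planned; each task compares barefoot with shod participants.

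These limits stand. Two further objections carry less weight. Foot strike is one outcome among several with no primary outcome named, which limits the reach of the point but does not make the criterion valid. Details of confounder selection are often left to an analysis plan, but here the article states the rule, its threshold and its scope, so this is not a missing detail. The unstated link does not rescue the rule either, since a probit coefficient rescales in the same way.

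**Conclusion.** The point holds in a limited form. As written, the 10 % rule is not a valid test of confounding in the ordinal foot-strike models, because the coefficient change adds a scale shift to any confounding. The harmful case is a confounder of moderate to strong effect and modest imbalance that exaggerates the group difference. Such a confounder can go unflagged when the same confounding would pass 10 % in a linear model.

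The figures rest on the assumed logit link, group log odds ratio, strike shares and covariate effects, and they ignore the school effect. Whether any of the five covariates falls in the masking region cannot be settled from the documents. Gender, BMI and PAQ score are likelier to be only modestly imbalanced than ethnicity or test location. The point concerns foot strike only and makes no claim about the linear models. It is worth correcting because the stated rule can leave out a real confounder and the remedy is cheap.

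**What to change.** In Statistical analysis, limit the 10 % rule to the linear models. Add one sentence: the ordinal models for foot strike in jogging and in sprinting will both be adjusted for gender, BMI, PAQ score, ethnicity and inside/outside testing, whatever the change in the coefficient. This also brings these models into line with the Discussion, where ethnicity is simply adjusted for. The planned test of gender as an effect modifier can stay.

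The cost is a few degrees of freedom, which is small at n = 520, and some loss of precision where a covariate closely follows country, as ethnicity and inside/outside testing may. All five covariates are already planned, so no new data are needed. Reporting standardised rearfoot, midfoot and forefoot proportions by group beside the odds ratios would help readers but is optional.

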### Participants

After pilot testing for reliability and validity of the measurement apparatus, recruitment of participants exclusively will take place in rural and urban primary and secondary schools with no restriction to school type. In South Africa, primary school attendees are aged 6–13/14 and secondary school children are between 13/14–18 years old, their German counterparts are 6–9/10 and 9/10–18. With approval from the German and South African supervisory school authorities, schools will be randomly selected per stratum (representing a combination of district and type of school) and contacted by the principal investigators. Schools (in blocks of five primary schools and five secondary schools) will be initially contacted via email and when interested visited by the study staff for further organisation. If the school wants to participate, consent forms for all pupils (and their parents) will be provided in the appropriate language (English, Afrikaans, Xhosa or German, Additional file 1). No limit will be set per school for maximum number of participating children per age. We will strive for an equal distribution of portion of participants per school to ensure equal representation. For participation, pupils will be requested to bring along the signed consent form on the testing day.

Inclusion criteria will consist of healthy children that are physically active for at least 120 accumulative minutes per week (parent reported). Children and young adolescents between the age of 6 and 18 will be recruited for this study. Exclusion criteria will be evaluated by parent proxy report and consist of current injuries of the lower extremity, abnormal gait or any neurological or neuromuscular abnormalities likely to influence the gait.

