### Sample size

Although we did not opt to distinguish primary or secondary outcome measures, the dAI was used to enable a sample size calculation. Muller et al. [36] has shown that the average dynamic arch index (μ: 0,19) and the accompanying standard deviation (SD: 0065) are stable between the ages of 6 and 13. The minimal important difference was set at 20 % of the average (0.19; i.e., 0.038). With a two-sided significance level of 0.05, and assuming a power of 0.8, a minimum of 16 participants per age group, per country, had to be included for this study. Due to the diversity of the study, additional power calculations have been performed. Based on the arch height ratio derived from Waseda et al. [22] the sample size for arch height ratio (navicular height*100/foot length) should be *n* = 12 per age group (μ = 15,0; SD = 2,6). Furthermore, based on a preliminary study on children, the sample size based on the standing long jump should be *n* = 18 (μ = 152,9; SD = 31,5), for lateral jumping *n* = 22 (μ = 38; SD = 9,2) and for 20 m sprint *n* = 12 (μ = 3,81; SD = 0,64). Therefore, our *n* = 20 per group seems to be sufficient. In order to allow for these differences and other unknown variances within the other variables we choose to increase the number from 16 to 20 participants per age group, per country.

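### The protocol expects older boys to differ but plans no age-by-gender term, so a gender mix that differs between barefoot and shod children at older ages would partly enter the age-by-group test

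*Protocol article*

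**What the plan says.** The second aim, stated in the Background and repeated in the Discussion, is whether barefoot-shod differences depend on age. Under Statistical analysis it is tested by "adding an interaction of age*group to the linear regression". This is the only interaction with age that is named.

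Gender has two roles in the same section:

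- Candidate confounder: "Gender, BMI, PAQ-Score, ethnicity and inside/outside testing will be tested for confounding in all models (regression coefficient changes >10" per cent.
- Effect modifier: "gender will additionally tested as an effect modifier (interaction between outcome and gender *p* < 0.1". The sentence literally pairs outcome with gender, but its opening clause makes clear that gender is to modify the effect of being barefoot or shod.

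The section also lists expected covariate directions, including "We hypothesize that older boys could have higher arches (lower dAI) [37] and perform better on motor performance tasks". The expectation for girls' pliability in that sentence has no age qualifier.

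On recruitment, the Sample size section decides to "increase the number from 16 to 20 participants per age group, per country". The Participants section says that "schools will be randomly selected per stratum (representing a combination of district and type of school") and that "No limit will be set per school for maximum number of participating children per age". Neither section mentions a gender split within age cells.

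**The concern.** If boys pull ahead of girls only in the older ages, a single gender coefficient describes the gap averaged over 6 to 18 years. It over-corrects young children and under-corrects adolescents. The gender-by-group term does not help, because it lets the barefoot effect differ by gender but not the gender gap by age.

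The uncorrected part matters for age-by-group only if the gender mix changes with age differently in the two groups. A higher share of boys among older barefoot children than among older shod children would then look like a barefoot advantage that grows with age, which is the pattern the second aim looks for. Jump and sprint are the most exposed outcomes. Under the 10 % rule gender may also be left out altogether, and then nothing is corrected.

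**Working it through.** **Design figure.** Ages 6 to 18 give 13 ages, and 13 x 20 x 2 countries = 520, which matches the stated total. How the 20 per cell was justified does not enter this check.

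**Inputs not in the article (assumed).** The size of the age-by-gender effect and the share of boys in each cell. Both are varied below. All simulations use 20 children per age per group, treat group as country, have no true group effect and leave out the school random effect.

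**Step 1. What chance does.** For one pair of cells of 20, the SD of the difference in boys' share is sqrt(2 x 0.25/20) = 0.158, so the 95% range is 1.96 x 0.158 = 0.31, or 31 percentage points. The age-by-group test pools ages, however. Over ages 14-18 there are 5 x 20 = 100 children per group, and the SD is sqrt(2 x 0.25/100) = 0.071. A 15-point gap in one direction is then 0.15/0.071 = 2.1 SD, and a 30-point gap is 0.30/0.071 = 4.2 SD. Sustained gaps of that size need a systematic cause.

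**Step 2. Standardised simulation.** Boys' advantage rises linearly from 0 at age 12 to 1.0 SD at age 18. Boys' share is 0.5 up to age 12 and as shown from age 13. There were 3,000 runs per setting, so the simulation error at 5% is sqrt(0.05 x 0.95/3000) = 0.4 points. Entries are the rejection rate for age-by-group and, in brackets, the false change in the group difference from age 6 to 18 in SD units.

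| Boys' share, barefoot/shod | No gender term | Gender main effect | Gender + age-by-gender |
|---|---|---|---|
| 0.5/0.5 | 5.4% (0.01) | 5.3% (0.01) | 4.3% (0.00) |
| 0.7/0.7 | 5.3% (0.01) | 5.1% (0.01) | 5.5% (0.01) |
| 0.6/0.5 | 6.4% (0.10) | 5.8% (0.07) | 5.1% (0.01) |
| 0.7/0.5 | 11.0% (0.20) | 7.7% (0.12) | 5.2% (0.03) |
| 0.7/0.3 | 28.6% (0.40) | 15.7% (0.28) | 5.6% (0.05) |

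The first two rows show that the test keeps its level when expected shares are equal, even if both groups hold 70% boys. At 0.7/0.5 the main effect removes (0.20 - 0.12)/0.20 = 40% of the bias, and at 0.7/0.3 it removes (0.40 - 0.28)/0.40 = 30%. With an advantage of 0.5 to 1.5 SD at age 18, the 0.7/0.5 main-effect rate runs from 5.7% to 10.0%. The small bias left in the last column arises because a linear term does not fit a gap that starts at age 12.

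**Step 3. Standing long jump scale.** Assumed: no gap to age 11, rising to 20, 40 or 60 cm at 18, and boys 65-80% of barefoot cells at 14-18 against 50% of shod cells. The planned model is given both gender and gender-by-group.

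- Residual SD 20 cm (assumed): rejection about 6-48%, false slope 0.16-1.03 cm per year, or 12 x 0.16 = 1.9 to 12 x 1.03 = 12.4 cm from age 6 to 18.
- Residual SD 31.5 cm (the SD in the Sample size section, which may include age spread): about 4-27%.
- No gender term, as the 10 % rule permits, SD 20 cm: about 9-75%.
- Age-by-gender added: about 4-6%.

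The 48% needs a 60 cm gap, an 80% v 50% split and the smaller SD together.

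**Step 4. Cost with no imbalance.** At SD 20 cm the slope standard errors with the main effect only are 0.48, 0.50 and 0.54, against 0.47, 0.48 and 0.49 with age-by-gender. The ratios are 1.02, 1.04 and 1.10. Across runs the loss is about 1-10%.

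**The case against.** The strongest reply is that nothing in the article says the gender mix will differ. Schools are drawn at random within strata and consent forms go to all pupils. This stands. The barefoot rule does change at secondary school, so older barefoot children are selected differently from younger ones, but the article gives no sign that this selection depends on gender.

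A reader might infer that any gender imbalance at older ages biases the test, or that the 31-point chance range for a pair of cells produces the high error rates. Neither follows. Shared imbalance is harmless, and chance imbalance over pooled ages leaves the level near 5%. The high rates come from an assumed systematic split.

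It is also fair that the sentence on older boys is tentative, sits in a list of covariate expectations and could be read as separate age and gender effects. No gender expectation is stated for foot strike or hallux angle, so a demand for the term in every model would go beyond the text.

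Finally, covariate interactions are often left to an analysis plan. Here, though, the article itself lists its interactions and its expectations, and the two do not match.

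**Conclusion.** The mismatch is real, and its consequence is conditional. The stated model does not carry the age-dependent gender effect that the protocol most naturally anticipates, and recruitment does not guard against a differential gender mix. Whether the age-by-group test is biased depends on a mix that the article neither reports nor prevents, so the documents do not support saying that the planned test is biased.

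With equal expected shares, the loss is about 1-10% in standard error. Under an assumed systematic 65-80% v 50% share, false positives are about 5-30% in most settings and about 40-50% only in the most extreme. The gender gaps, the shares, the 20 cm residual SD and the omission of school clustering are all assumptions. Priority is minor to moderate.

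**What to change.** In the arch and motor performance models that test age-by-group, include gender and age-by-gender as fixed terms whatever the 10 % rule would decide, alongside the planned group-by-gender test. Report the number of boys and girls by age and group, so that readers can see whether the mix differed.

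The cost is one line in the analysis section and one degree of freedom per model if age is linear. If the 13 ages are categories, the term takes 13 - 1 = 12. A gender quota per age-by-country cell is optional and might slow the filling of the last cells slightly.
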